A research midwife will contact women at 8 weeks postnatally to provide a dedicated Slimming World® (Alfreton, UK) telephone number for member services. A Slimming World® (Alfreton, UK) consultant will provide the woman with information on the local groups she can join, times, and venue (standard practice). Women can choose which group they attend and when they commence groups within the 8 to 16 week ‘window’ to fit with their health, lifestyle, and family demands. Women can take their babies with them.

We will assess adherence to allocation protocols, loss to follow-up, and women’s views of acceptability and sustainability. To capture data on whether women attend for each complete Slimming World® (Alfreton, UK) group session or leave after the initial weigh-in, we will ask women to complete in their follow-up questionnaires how many groups they attended and stayed for the whole session. Follow-up will capture data on women who continue attending groups or achieve their goal and stop attending to compare outcomes of interest with the control group.

Slimming World’s® (Alfreton, UK) quality assurance procedures ensure standardisation of weight management groups, including weekly calls between group consultants and their team managers. As consultants are from the local area, they will be aware of cultural preferences, time, and budget constraints women face and can advise on basic cooking skills and local shops selling healthy foods within women’s budgets. The Food Optimising system used in Slimming World® (Alfreton, UK) groups includes pictorial use of recipes for individuals who may not have a high level of understanding of written English. As our postnatal population is geographically mobile [31], women who move from the area can transfer their group membership to another local group anywhere in the UK.

Women from both trial groups will be asked to attend an appointment with a research midwife to be weighed either at the study site or at their home at 6 and 12 months. Travel costs and £10 Love2Shop voucher to thank women for their time will be offered.

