### Trial feasibility objectives

The primary feasibility objective is to estimate the effect size for a likely primary study outcome in a future definitive trial, namely difference between study groups in weight change from booking to 12 months postbirth, expressed as percentage of weight change or weight loss in kilogrammes. Mean percentage change across all women gives greater power, and fewer women will need to be recruited. We will undertake pre-planned sub-group analysis of the primary assessment in women of different booking BMI categories. The primary endpoint for a future trial will be selected on grounds of power.

Other objectives include those most appropriate to support meeting the primary objective and inform progress to a definitive RCT. These will include rates of 5% and 10% weight reduction and changes in relation to aspects of healthy lifestyle and health behaviours, including diet and nutrition, breastfeeding, physical activity, smoking cessation, alcohol intake, self-esteem, and body image. Some included measures have been validated in relevant populations, including among women of reproductive age and women who have recently given birth.

Measures will be included in questionnaires at 6 and 12 months postnatally. Those marked with ‘**’ will also be included in the baseline questionnaire. Questionnaires will be ‘tailored’ for the intervention or standard care arm, to enable questions on uptake of support for weight management to be included at 6 and 12 months to inform trial process outcomes:
Dietary intake: The Dietary Instrument for Nutritional Education (DINE© University of Oxford)** [33]Soft drink intake: questions developed for the studyPhysical activity: The International Physical Activity Short-Form** [34]Mental health: Edinburgh Postnatal Depression Scale [35]Breastfeeding intent**, uptake, and duration, questions developed for studySleep patterns: questions developed for the studySmoking: smoking status/cigarette dependence** [36]Alcohol consumption: Alcohol Use Disorders Identification Test** [37]Self-esteem: Rosenberg Self-Esteem Scale** [38]Infant health: questions developed for studyImpact on body image [39]Resource utilisation and costs outcome measures: the EQ-5D-5L** and the Adult Service Use Schedule** [40]

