### Trial process evaluation objectives

The process evaluation will focus on the following key aspects:
The acceptability of study processes and proceduresThe acceptability of the intervention and how it is experienced by women (those who complete at least 10/12 Slimming World® (Alfreton, UK) groups and those who do not; those who complete each group attended for the full session or leave after being weighed; those who continue to attend Slimming World® (Alfreton, UK) groups on completing the intervention and those who do not)The likely variation in groups attended by women in relation to date/time of day, and whether women stay with one consultant/group or try different groupsSources of weight management support control group women may have accessed; additional sources of weight management support intervention group women may have accessed

Data will be collected using questionnaires and semi-structured interviews with a sub-sample of women. Questionnaires at 6 and 12 months include sections designed to capture information on weight management views and use of strategies among all women, and on Slimming World® (Alfreton, UK) attendance, barriers, and facilitators among intervention women only.

Semi-structured qualitative interviews will be conducted at two time points with intervention women (*n* = approx. 10 women at 6 months; 15–20 at 12 months) to explore the acceptability and sustainability of the intervention, and acceptability of trial procedures. This will include targeting women who did and did not join Slimming World® (Alfreton, UK), those who did/did not attend the 12 sessions offered, and those who did/did not lose weight. At 12 months, a sub-sample of control group women will also be interviewed to explore study processes and experiences of participating, including reasons for taking part/dropping out, recruitment and randomisation (expectations/understanding of the study aims), views on outcome measures, attendance for weighing appointments as part of study follow-up, and lifestyle behaviours. Topic guides for both groups will be informed by the COM-B model of behaviour change [41], exploring barriers and facilitators to weight management/the intervention according to capabilities, opportunities, and motivations. Control group women will be asked about the impact, if any, of participating on their levels of physical activity or any dietary changes.

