### Sample size calculation, selection, and loss to follow-up

A sample size of 190 women will allow a 30% loss to follow-up to ensure we achieve our required sample size of 130 women. This study is designed firstly to establish the rates at which women could be recruited and retained in a future definitive RCT and estimate critical parameters with necessary precision to inform sample size requirements. In particular, we require estimates of the standard deviation, and design effect for the primary endpoint, allowing for clustering by intervention group. One hundred thirty women will allow estimates of the required sample size for any given clinically important difference to within 30% of the true value.

Based on published data [17, 42] the mean (SD) percentage weight change following a Slimming World® (Alfreton, UK) programme of 12 weekly groups is − 5.5% (3.3). Assuming these numbers are typical, 65 women in each group (130 in all) would be required to detect a difference of 2% between active and control groups with 90% power. Of around 6600 women who give birth at the reference maternity unit over 12 months in 2017, 40% were overweight, 15% of whom were obese. Data on women with excessive GWG are not routinely collated. Potentially, 55 women booking each week would meet obese/overweight inclusion criteria. Recruiting 7–8 women each week over an 8-month (32 week) period would be sufficient to achieve the desired sample size to meet the aims of this feasibility study.

Compliance issues are an important consideration. Loss to follow-up among postnatal women can range from 30 to 40% [43, 44]. Experience of research in similar populations has shown that planned initiatives including flexible follow-up appointments, travel expenses, vouchers for returning questionnaires, and sending of reminders can reduce loss to follow-up. Follow-up appointments will be offered at weekends and week days, with the option to complete questionnaires at these appointments.

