### Analysis

Process data will be analysed separately before examining relationships between quantitative and qualitative data, with synthesis completed in line with O’Cathain et al. [45]. Quantitative data will be entered onto the MedSciNet web-based data entry system. Retention and adherence will be considered from recruitment rate, consent rate, withdrawal and loss to follow-up (with reason), departures from randomised treatment, and prevalence of SAEs reported by treatment group and overall. Estimated differences and 95% confidence intervals will be calculated for specified primary and secondary analyses (significance at 5%). Sensitivity analyses will assess robustness of conclusions to missing outcome data and departures from randomised treatment. Analyses of potential efficacy will be based on the ITT sample, utilising follow-up data from all randomised women.

Differences between arms will be compared at 6 and 12 months postbirth adjusting for important prognostic factors (parity, maternal age, ethnicity, BMI at booking, and (as appropriate) baseline measurement). Data to inform process outcomes will be evaluated using descriptive analysis. Numbers (with percentages) will be presented for binary and categorical variables and means (standard deviations), or medians (with lower and upper quartiles) or geometric means for continuous variables will be presented. Stata version 15.1 or later will be used for analyses (StataCorp, College Station, TX).

Interviews will be recorded with women’s permission and transcribed and analysed using the framework method for thematic analysis [46]. Analyses will be deductively informed by the COM-B model for behaviour change [41]. Themes that emerge inductively will be captured, and efforts made to identify and explore disconfirming/outlier cases**.** Key topics and issues will be identified through familiarisation with transcripts by two researchers who will initially work independently and then together to discuss and agree the final coding framework with a third researcher. A series of thematic charts will be developed according to the coding framework, and data from each transcript summarised under each theme, enabling examination of similarities and differences of views within and between transcripts, and use of a constant comparative approach. Quantitative and qualitative data on acceptability of the intervention and other aspects of feasibility will be integrated using mixed-methods matrices [46].

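### The Interventions section plans to compare intervention women who keep attending, or who reach their goal, with the control group; this secondary contrast favours the intervention to the extent that either is related to weight loss

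*Protocol article*

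**What the plan says.** In the Interventions section, after explaining how attendance will be recorded, the protocol article gives a purpose for the follow-up data: they will cover "women who continue attending groups or achieve their goal and stop attending to compare outcomes of interest with the control group". Two intervention subsets are named and the comparator is the control group. The sentence does not mention women who never join or who stop without reaching their goal. It defines no matching control subset, does not call the comparison descriptive, and names no method for handling selection.

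Elsewhere the article is more careful:
- The primary feasibility objective concerns the "difference between study groups in weight change from booking to 12 months postbirth, expressed as percentage of weight change or weight loss in kilogrammes".
- The Analysis section states that "Analyses of potential efficacy will be based on the ITT sample, utilising follow-up data from all randomised women", and adds that "Sensitivity analyses will assess robustness of conclusions to missing outcome data and departures from randomised treatment".
- The process evaluation contrasts attendance groups within the intervention arm, on acceptability and experience. The groups include "those who complete at least 10/12 Slimming World" sessions and those who do not, and "those who continue to attend Slimming World® (Alfreton, UK) groups on completing the intervention and those who do not".

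**The concern.** Membership of either subset is decided after allocation. Goal achievers are identified by weight lost, which is closely tied to the outcome being compared. Continuers have chosen to carry on, and the Interventions section says they pay the weekly fee once the free sessions end. No such filter is applied to the control group, which keeps its less motivated women and those who lose little weight. The contrast therefore mixes any effect of the groups with the characteristics of the women who stay or succeed, and randomisation no longer protects it.

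At stake is a secondary result that could be read as the effect of attending, in a trial whose primary feasibility objective is to estimate an effect size. The intention-to-treat analysis is sound, but it does not correct a separate comparison made on a selected subset.

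**Working it through.** **Inputs from the document.** The sample size section gives a mean (SD) percentage weight change for a "programme of 12 weekly groups is − 5.5% (3.3"), so the SD is 3.3. It also says that "65 women in each group (130 in all) would be required to detect a difference of 2% between active and control groups with 90% power". Significance is at 5%, taken here as two-sided because the article does not say.

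**The plan's own figure, as background.** n per group = 2 × (1.960 + 1.282)² × 3.3² / 2² = 57.2, so 58 (59 with the t distribution). The stated 65 gives about 93% power, so it is conservative. It has no bearing on this point except to supply the 2-point yardstick.

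**Assumptions.** The document gives neither the fraction of intervention women who continue or reach goal (f) nor the correlation between that status and the 12-month outcome (ρ). Ranges are used: f = 0.3, 0.5, 0.7 and ρ = 0.3, 0.5, 0.7. The true effect is set to zero, outcomes are normal, and there are 65 women per arm with data.

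**Formula.** If the best fraction f on a marker with correlation ρ to the outcome is compared with all controls, the expected difference is

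bias = -SD × ρ × φ(z_f) / f,

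where φ is the standard normal density and z_f is the normal quantile at f. The factor φ(z_f)/f is 1.159 at f = 0.3, 0.798 at f = 0.5 and 0.497 at f = 0.7. For example, at f = 0.3 and ρ = 0.3 the bias is -3.3 × 0.3 × 1.159 = -1.15.

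**Results.** Each cell gives the bias in percentage points. In brackets is the simulated chance of a significant false benefit (5,000 runs per setting, t-test; nominal 2.5% in that direction).

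| f | ρ = 0.3 | ρ = 0.5 | ρ = 0.7 |
|---|---|---|---|
| 0.3 | -1.15 (26%) | -1.91 (61%) | -2.68 (91%) |
| 0.5 | -0.79 (19%) | -1.32 (47%) | -1.84 (77%) |
| 0.7 | -0.49 (12%) | -0.82 (25%) | -1.15 (45%) |

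At ρ = 0 there is no bias, and the false-benefit rate is about 2.3%. In the same simulations, comparing all intervention women with all controls gave two-sided rejection rates of 4.5% to 5.6%, in line with the nominal 5%. The bias is proportional to the SD, so a different SD for change from booking to 12 months would rescale every figure.

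**Check on an attendance analysis.** A binary cut-off at 10 of 12 groups would be a poor treatment variable in a complier-average causal effect (CACE) analysis, because it counts women attending 1 to 9 groups as untreated. As an assumed illustration, let 40% attend at least 10 groups with an effect of 2, and 30% attend 1 to 9 with an effect of 1. The intention-to-treat effect is 0.4 × 2 + 0.3 × 1 = 1.1. Dividing by 0.4 gives 2.75, although the effect in the women above the cut-off is 2. Using any attendance, 1.1 / 0.7 = 1.57, which is the average effect among attenders.

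**The case against.** The strongest reply is that the sentence describes data collection. It sits in the Interventions section, among remarks on what the questionnaires record, and it defines no endpoint, model or estimand. It could mean only that women still attending and women who have stopped will both be followed up. No analysis section repeats the comparison. Efficacy is intention-to-treat on all randomised women, and the only pre-planned sub-group analysis of weight is by booking BMI. The process evaluation already handles attendance contrasts within the intervention arm.

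Much of this stands, and it limits the point to one secondary comparison. It does not remove it: the sentence gives comparison with the control group as the purpose and names only two favourable subsets. If description is all that is meant, the text should say so.

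The lack of a named estimator for departures from randomised treatment is not a fault. That detail commonly belongs in the statistical analysis plan.

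A reader might also infer that the effect size carried into the definitive trial, or the decision to progress, would be inflated. The document does not support that. The effect size is defined as the difference between the randomised groups, and no success criterion in Table 1 uses outcomes in attenders.

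**Conclusion.** The point holds as a correction to one sentence. Followed as written, the comparison is biased towards the intervention whenever continuing or reaching goal is positively related to weight loss. Under the assumed fractions and correlations the bias runs from about -0.5 to -2.7 points, so under stronger selection it matches or exceeds the 2-point difference used for sizing. The size cannot be computed from the document; f and ρ are assumptions.

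Two stronger readings should be resisted. First, benefit is not certain to appear under no effect: with zero correlation there is no bias. Second, the whole subset is not selected on the outcome itself. That applies at most to goal achievers; for continuers the selection is on adherence. Even for goal achievers the link is imperfect. The goal is not defined, the groups start 8 to 16 weeks after birth, and the outcome runs from booking to 12 months, so a woman may reach her goal and regain weight. Treating the subset as exactly the best 30% on the outcome gives 1.159 × 3.3 = 3.8 points, which is an extreme case rather than an expectation.

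**What to change.** Reword the sentence in the Interventions section so that all between-arm outcome comparisons use all randomised women, as the Analysis section already requires. Describe continuers, goal achievers and women who stop within the intervention arm only, as the process evaluation does.

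If an effect of attendance is wanted, use an instrumental-variable (CACE) analysis with randomised allocation as the instrument. Take number of groups attended, or any attendance versus none, as the treatment variable, and avoid the binary 10-of-12 split. State the assumptions: the leaflet alone has little effect on weight and, if number attended is used, the dose-response is roughly linear.

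The cost is one reworded sentence and, if the attendance question is kept, one extra model with a wider interval than the intention-to-treat estimate.

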### Standard care

Women allocated to standard care only will receive standard NHS maternity care to 8 weeks postnatal. This could include, for example, routine midwifery and health visitor contacts for infant feeding assessment and assessment of birth recovery. Women will be offered a routine contact with their GP at around 6–8 weeks postnatally. We will ask all recruited women at their 6 and 12 month follow-up about their experiences of using weight management groups or other sources of support for weight management, healthy lifestyle, and activity.

### Trial objectives

Feasibility objectives reflect MRC guidelines for complex interventions [32] with important exceptions. The aim is not to evaluate the intervention itself. Slimming World® (Alfreton, UK) groups are ‘standardised’, with robust mechanisms to ensure intervention fidelity. Our process evaluation is not designed to answer some questions seen in complex evaluations regarding generalizability of the intervention, assurance that implementation/delivery of the intervention is consistent across sites, or determine mechanisms of impact. This study reflects a pragmatic trial approach—evaluating the impact of an intervention where women can choose which group to attend and can switch groups, exactly as if they were a ‘standard’ self-referred member of Slimming World® (Alfreton, UK).

### Trial feasibility objectives

The primary feasibility objective is to estimate the effect size for a likely primary study outcome in a future definitive trial, namely difference between study groups in weight change from booking to 12 months postbirth, expressed as percentage of weight change or weight loss in kilogrammes. Mean percentage change across all women gives greater power, and fewer women will need to be recruited. We will undertake pre-planned sub-group analysis of the primary assessment in women of different booking BMI categories. The primary endpoint for a future trial will be selected on grounds of power.

Other objectives include those most appropriate to support meeting the primary objective and inform progress to a definitive RCT. These will include rates of 5% and 10% weight reduction and changes in relation to aspects of healthy lifestyle and health behaviours, including diet and nutrition, breastfeeding, physical activity, smoking cessation, alcohol intake, self-esteem, and body image. Some included measures have been validated in relevant populations, including among women of reproductive age and women who have recently given birth.

Measures will be included in questionnaires at 6 and 12 months postnatally. Those marked with ‘**’ will also be included in the baseline questionnaire. Questionnaires will be ‘tailored’ for the intervention or standard care arm, to enable questions on uptake of support for weight management to be included at 6 and 12 months to inform trial process outcomes:
Dietary intake: The Dietary Instrument for Nutritional Education (DINE© University of Oxford)** [33]Soft drink intake: questions developed for the studyPhysical activity: The International Physical Activity Short-Form** [34]Mental health: Edinburgh Postnatal Depression Scale [35]Breastfeeding intent**, uptake, and duration, questions developed for studySleep patterns: questions developed for the studySmoking: smoking status/cigarette dependence** [36]Alcohol consumption: Alcohol Use Disorders Identification Test** [37]Self-esteem: Rosenberg Self-Esteem Scale** [38]Infant health: questions developed for studyImpact on body image [39]Resource utilisation and costs outcome measures: the EQ-5D-5L** and the Adult Service Use Schedule** [40]

### Trial process evaluation objectives

The process evaluation will focus on the following key aspects:
The acceptability of study processes and proceduresThe acceptability of the intervention and how it is experienced by women (those who complete at least 10/12 Slimming World® (Alfreton, UK) groups and those who do not; those who complete each group attended for the full session or leave after being weighed; those who continue to attend Slimming World® (Alfreton, UK) groups on completing the intervention and those who do not)The likely variation in groups attended by women in relation to date/time of day, and whether women stay with one consultant/group or try different groupsSources of weight management support control group women may have accessed; additional sources of weight management support intervention group women may have accessed

Data will be collected using questionnaires and semi-structured interviews with a sub-sample of women. Questionnaires at 6 and 12 months include sections designed to capture information on weight management views and use of strategies among all women, and on Slimming World® (Alfreton, UK) attendance, barriers, and facilitators among intervention women only.

Semi-structured qualitative interviews will be conducted at two time points with intervention women (*n* = approx. 10 women at 6 months; 15–20 at 12 months) to explore the acceptability and sustainability of the intervention, and acceptability of trial procedures. This will include targeting women who did and did not join Slimming World® (Alfreton, UK), those who did/did not attend the 12 sessions offered, and those who did/did not lose weight. At 12 months, a sub-sample of control group women will also be interviewed to explore study processes and experiences of participating, including reasons for taking part/dropping out, recruitment and randomisation (expectations/understanding of the study aims), views on outcome measures, attendance for weighing appointments as part of study follow-up, and lifestyle behaviours. Topic guides for both groups will be informed by the COM-B model of behaviour change [41], exploring barriers and facilitators to weight management/the intervention according to capabilities, opportunities, and motivations. Control group women will be asked about the impact, if any, of participating on their levels of physical activity or any dietary changes.

Telephone or face to face interviews will be offered. Sampling will be based on maximum diversity in relation to age, parity, ethnicity, and socio-economic status and reflect the range of weight loss/gain of the sample.

